#### Tailoring Variables

Tailoring variables are information about the participant that is used to decide when to provide which intervention. In other words, they are used to personalize the interventions and make them adaptive to the individual’s circumstances. All proximal outcomes can serve as tailoring variables. They can be measured actively, passively, or both. Active assessments require an individual's engagement in measuring, for example through self-reports, while passive assessments require minimal or no individual engagement, for example through a mobile phone’s sensors.

From baseline information, we can select a few tailoring variables, including alcohol consumption, smoking, specific diet, age, and gender, in order to personalize the interventions. These are considered to be hard-pruning because, with the help of these baseline tailoring variables, a set of intervention options are ruled out from the beginning. As an example, if the person is a nonsmoker, there is no need to motivate him or her to quit smoking.

From the MUAH-16 questionnaire, we start to learn more about an individual’s beliefs, barriers, and behavior about MA. It has 4 subscales regarding (1) positive attitude toward health care and medication, (2) lack of discipline, (3) aversion toward medication, and (4) active coping with health problems. Each subscale contains 4 questions. At the beginning of the intervention, MUAH-16 questions are used as tailoring variables. Then, during the intervention period, and based on the previously delivered informational contents to the individual, the answers to “Did you know...?” questions will be used as tailoring variables.

#### Decision Rules

Decision rules are the adaptation engine of JITAIs. They are used to determine which intervention option to deliver to whom and when. They are the links between intervention options and tailoring variables. Operationally, a JITAI includes a sequence of decision rules (ie, treatment policies) that take the individual’s current context as input and specify whether an intervention should be delivered now and what intervention should be delivered [45].

Decision rules in iMedA will be probabilistic rules from experts modified by “suggestions” from reinforcement learning [46]. Reinforcement learning is used to continuously learn and optimize the treatment policy in JITAI as the individual experiences the interventions. It automatically “discovers” which interventions are most successful for which patients by using statistical machine learning methods.

Since we are using an interrupted time series design, we will consider the first 14 days after the app installation to be the preintervention phase (ie, data collection). Figure 2 shows the flowchart of these initial 14 days in more detail.

**Figure 2 figure2:**
[figure not shown]
An illustration of the preintervention step (ie, the first 14 days). HL: health literacy; MUAH-16: 16-item Maastricht Utrecht Adherence in Hypertension; QoL: quality of life.

At the beginning of the intervention delivery, the JITAIs will be delivered based on expert suggestions, taking into account the answers to the initial questionnaires, to provide baseline data that a reinforcement learning agent can use to improve upon without the necessity for a warm-up period characterized by random interventions. To allow the agent to learn effectively from collected data, the expert decision rules will be defined in a probabilistic manner, allowing off-policy evaluation. The agent will be built upon a contextual bandit framework that uses tailoring variables to adaptively suggest interventions to improve proximal outcomes and, ultimately, distal outcomes. The agent will optimize the decision rules on a biweekly basis, allowing evaluation before deployment, as illustrated in Figure 3.

**Figure 3 figure3:**
[figure not shown]
An illustration of the intervention phase. PA: physical activity; RL: reinforcement learning; RP: random policy.

##### Contextual Bandit Formulation

The decision rules update is scheduled every 14 days, and the policy (decision rules) remains unchanged during the 2 weeks between each update. With the previous data (tailoring variables, interventions, query-responses) collected, the agent’s policy is updated to personalize interventions for individual patients. We formulate the learning of an optimal policy for a given patient as a stochastic contextual bandit problem. Traditionally, the problem is specified by a tuple (S, A, R) where *S* is the context space (tailoring variables), *A* is the finite action-space (number of interventions), and *R* is the rewards (query-responses). Only rewards of the chosen action are known to the agent at a decision point; rewards of other actions are unknown. Through interactions with the patient, at every decision point at time t, the agent has a sequence of tuples *D* = {(*S*_0_, *A*_0_, *R*_0_), (*S*_1_, *A*_1,_
*R*_1_), ... , (*S_t_*_−1_, *A_t_*_−1_, *R_t_*_−1_)} available to make decisions. *D* is known as the interaction history, containing the context and actions (interventions) chosen by the agent as well as reward received up until *t*−1.

We make several simplifying assumptions necessary for optimal learning:

###### Assumption 1

The stochastic bandit formulation assumes identically and independently distributed contexts, therefore action *A_t_* does not affect the distribution of future contexts *S*_τ_ for τ > *t* + 1.

In simpler terms, the agent does not affect the contexts (tailoring variables) we observe from patients. The effect of each intervention is limited in time, such that we can adjust to changes in behavior gradually.

###### Assumption 2

The expected reward (query-responses) of an action (intervention) can be modeled by an arbitrary (often linear) function *f*:*S* × *A* → *R* for all t such that the expected (average) reward for an action in a particular context can be predicted as:

In our formulation, we assume that the context allows an informative mapping from contexts and actions to reward (ie, the reward we would receive for an intervention can be predicted and therefore allows the optimal action to be selected for a particular context).

We cast the learning of function *f*(∙) as a binary classification problem where the probability outputs directly correspond to the expected reward given context *S_t_* and action *A_t_*. At every decision point t, the agent follows a greedy action selection strategy, that is, the agent selects action *A_i_* with the highest predicted reward *f*(*S*_t_, *A_i_*) given the current context:

*A_t_ = π_B_*(*S_t_*) **(2)**,

where *π_B_* is greedy policy, defined as 

.

To facilitate occasional exploration, action *A_t_* is chosen by an *ε*-greedy strategy that randomizes action selection irrespective of current context with probability *ε* ∈ (0,1]. At each time step, either a random action (with probability *ε*) or the action with the maximum predicted reward (with probability 1−*ε*) is chosen.

##### Policy Update

The policy *π_B_* is updated every 14 days using the data collected by the agent thus far by estimating the parameters of function *f*(*S*, *A*). To evaluate new and better policies before deployment, we use importance sampling in combination with the updated reward predictor *f*(*S*, *A*) to estimate the expected reward under the new policies. More formally, given a policy *π_B_* used to collect the past data *D* and the current tuple (*S_t_*, *A_t_*, *R_t_*) forming data set *S* = *D* ∪ (*S_t_*, *A_t_*, *R_t_*), we estimate the expected reward of target policy *π_T_* in combination with the updated reward predictor *f*(*S*, *A*), using the doubly robust estimator [47]:

where I(*π_T_*(*S*) = *A*) is an indicator function, being 1 if action *A* is chosen under target policy *π_T_* and 0 otherwise. 

 is the probability of choosing an action under the old policy *π_B_*, which is known. For a set of policies Π, we choose the policy that maximizes the average policy reward 

:

The new policy *π_new_* is then deployed with the *ε*-greedy strategy.

#### Decision Points

A decision point is a time when an intervention decision is made. Considering the nature of JITAIs that are delivered through mobile devices, decision points occur much more rapidly than in standard interventions.

In iMedA, every day the intervention is delivered accompanied by the time of medication intake question (ie, “It is time to take your medication <medication name>. Did you take it today?”). If the patient has >1 antihypertensive dose per day, then the decision point will happen in only one of those reminders.

These daily interventions are chosen from a 14-day intervention list that the reinforcement learning agent has picked. However, the decision rules are updated every 2 weeks, meaning that the reinforcement learning agent will optimize the decision rules to be adapted to the patient's needs after 14 days of looking into the patient's behavior.

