#### Longitudinal Study

The data from the participants in the study are sent through their mobile app to the server, where all the participants’ data is stored. All the data from the participants are collected via self-reports and their hypertension-relevant information in the aggregated health database. The only item that we measure without the participants’ engagement is if they have seen the intervention and how long it took to answer the questions. This information is used to measure the user’s fatigue and intervention retention and will be used to adapt the interventions.

The effect of the intervention is analyzed statistically using segmented regression analysis, testing for changes in both the level and the trend of the outcome.

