#### Intervention Options

Intervention options are a set of possible interventions that are going to be delivered at decision points. In JITAI, intervention options can be various types of support (information, advice, feedback, etc), source of support (mobile, nurse, physician, etc), amounts of support (intensity, dose, etc), and type of media or channel (phone call, SMS text messaging, etc).

From the conducted literature review, we summarized all types of digital interventions delivered to individuals with hypertension as follows: (1) reminders for medication intake (daily or several times per day depending on the antihypertensive medication plan), reminders for BP measurement (every 3 months), and reminders for physical activity (biweekly); (2) informational contents regarding hypertension and all its facts, consequences, treatments, risks, medications and side effects, lifestyle, and so on (text, videos, etc)—the prepared interventions will be based on health care professional advice plus the reference of webpages for further readings; (3) trends on medication intake, physical activity, etc in a feedback motivational message—based on the recent activity of the user, a feedback motivational message is sent biweekly; and (4) motivational messages—the relevant messages are phrased in a motivated manner (eg, regarding smoking, a message like “Treatment of high blood pressure has a much better effect if you do not smoke.”).

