#### Distal Outcomes

Distal outcome is the ultimate goal that the intervention is trying to achieve. In iMedA, we considered primary and secondary distal outcomes. Primarily, we aim at improving MA. Then, in the long term, BP is considered as a secondary distal outcome along with increased quality of life [42], assessment of the lifestyle behavior (smoking, alcohol consumption, physical activity, and food intake) [10], and communicative and critical health literacy [43].

In order to measure MA, we consider the following:

Self-reported medication intake through the mobile app is supposed to be collected every day.MUAH-16 [44] is measured before and after the intervention. It is a MA questionnaire for hypertension. It consists of 16 items with four factors: (1) positive attitude towards health care and medication, (2) lack of discipline, (3) aversion toward medication, and (4) active coping with health problems. The items are on a 7-point Likert scale (1=completely disagree to 7=completely agree). A previous study [44] had found correlations between adherence and the MUAH-16 score. Specifically, they found that higher scores in subscale 1 correlated positively with adherence, and higher scores on subscale 2 correlated negatively with adherence.Pickups from pharmacies will be collected after the intervention is finished.

BP is to be measured once before the start of the intervention, at 3 months, and then at 6 months by the recruited nurse.

Health literacy will be measured by the Swedish Communicative and Critical Health Literacy scale. It consists of 5 items with a 5-point Likert scale [43]. Health status will be measured by EQ-5D (EuroQol 5-Dimension questionnaire). It consists of 5 areas for covering health, with 5 response alternatives and 1 overall question regarding health (EQ-VAS [EuroQol visual analogue scale] with score range of 0 to 100) [42]. Both will be measured before and after the intervention.

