#### Proximal Outcomes

Proximal outcomes are the short-term goals of the interventions. They can be mediators, intermediate measures, or both for the distal outcomes. The medication intake is considered to be the main proximal outcome, which is measured daily. The physical activity rate, which is measured weekly, is another proximal outcome.

Since most of the contents are educational, and they try to increase the hypertension knowledge of the participants, we will add a proximal outcome to measure how much their knowledge has increased. We consider two methods to measure it. First, after showing the content, we will ask “Did you know...?”. Second, we will design simple gamification tests to be presented to the participants biweekly.

To prevent poor adherence to the interventions, it is recommended to define a few proximal outcomes related to intervention engagement and fatigue. Therefore, we consider the number of clicked interventions, dwell time, number of watched videos, and like/dislike feedbacks for each intervention as proximal outcomes related to intervention adherence and retention.

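### The daily intake question names the drug and the day but not the scheduled dose, and is asked as the dose falls due, so it can misrecord intake

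*Protocol article*

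**What the plan says.** The article's Decision Points section gives the intake question in full: "It is time to take your medication <medication name>. Did you take it today". The same message tells the participant that a dose is due and asks whether it was taken.

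The article foresees more than one dose a day. Intervention Options lists "reminders for medication intake (daily or several times per day depending on the antihypertensive medication plan", and Decision Points adds: "If the patient has >1 antihypertensive dose per day, then the decision point will happen in only one of those reminders". Only the decision point, meaning the choice of what content to deliver, is limited to one reminder. Nothing limits the intake question in that way.

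The answers have two uses. Under Distal Outcomes they are one of three measures of medication adherence, the primary outcome: "Self-reported medication intake through the mobile app is supposed to be collected every day". The other two are less frequent: MUAH-16 is completed before and after the intervention, and pharmacy pickups are collected once it has finished. Under Proximal Outcomes: "The medication intake is considered to be the main proximal outcome, which is measured daily".

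The Longitudinal Study section under Data Collection and Analysis says that the app also logs "how long it took to answer the questions", and gives the purpose as measuring fatigue and retention and adapting the interventions.

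**The concern.** As a measuring instrument the item has two ambiguities, both arising from its wording and timing.

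1. **Which dose.** The question covers the drug and the whole day. With two daily doses of the same drug, yes at the second reminder is true as soon as the first dose has been taken, whatever happens to the second.
2. **Which moment.** The message says the dose is due now, yet asks in the past tense about a day that is not over. A participant who replies at once and then takes the tablet gives a true no on a day when the dose was taken.

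The study is an interrupted time series on daily data, analysed for changes in level and trend by segmented regression. This is the only adherence measure collected daily, so it appears to carry the within-person series for the primary outcome. An analysis plan can set scoring rules afterwards, but it cannot recover which dose a yes referred to if the question never asked.

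**Working it through.** The document states no figure for the accuracy of this item, so there is nothing to reproduce. The check is a reading of the sections side by side, followed by an illustration on assumed values.

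**Reading**

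- Decision Points: the item specifies drug and day, not dose, and is shown at the time of intake.
- Intervention Options and Decision Points: several reminders a day are expected for some participants, so the wording must also serve them.
- A second dose of a *different* drug has its own named prompt, so it can be told apart. A second dose of the *same* drug cannot be told apart from the wording alone.
- Longitudinal Study (data collection): time to answer is logged, so a reply may come after the prompt, and possibly after intake.
- Not stated: the response window, whether an answer can be changed, the scoring of no, late or absent answers, the share of participants on several daily doses of one drug, and the share who reply before taking the dose.

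**Illustration 1: two daily doses of the same drug.** Assume independent doses, each taken with probability p. The first prompt is answered correctly for its own dose; the second is answered literally, as any dose today.

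- Probability of at least one dose: 1 − (1 − p)²
- Recorded adherence: [p + 1 − (1 − p)²] / 2
- Overstatement: recorded − p = p(1 − p) / 2

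| Assumed p (true) | At least one dose | Recorded | Overstatement (points) |
|---|---|---|---|
| 0.5 | 0.75 | 0.625 | 12.5 |
| 0.7 | 0.91 | 0.805 | 10.5 |
| 0.8 | 0.96 | 0.88 | 8 |
| 0.9 | 0.99 | 0.945 | 4.5 |

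A more extreme pattern, with the first dose always taken and 40% of second doses missed, gives true adherence of (1.0 + 0.6) / 2 = 0.80 against 1.00 recorded. If each prompt is answered for its own dose, the overstatement is 0.

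**Illustration 2: reply before intake.** Assume true adherence of 0.90 and a share q of taken doses that are taken after a no that then stands. Recorded adherence = 0.90 × (1 − q).

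| Assumed q | Recorded |
|---|---|
| 0 | 0.90 |
| 0.1 | 0.81 |
| 0.3 | 0.63 |
| 0.5 | 0.45 |

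If the reply waits until after intake, or the no can be corrected, the understatement is 0.

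The two errors run in opposite directions, and the document gives neither the share of same-drug multi-dose users nor q. No net figure follows.

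**The case against.** The strongest reply is that the message opens by saying a named medication is due, so most people will take the question to mean the dose now due. With a prompt for each dose and replies possible after a delay, the item may work well in practice. The wording is also a one-line English rendering for an app used by Swedish speakers. That app was still being built, and a pilot and usability focus groups lie ahead. Scoring and aggregation rules may properly stand in a fuller document. MUAH-16 and pharmacy pickups do not depend on the item, and the comparison with the control group uses pickups only. The learning agent's reward is described only as query responses, so it cannot be assumed to be this answer.

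Much of this stands, and it limits the point. A reader might infer more than the text supports in four respects:

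- *That a missed second dose cannot be recorded.* It can be: only the decision point is confined to one reminder, different drugs have their own prompts, and a participant may answer for the specific dose.
- *That a dose taken just after the prompt is scored as missed.* No scoring rule, response window or answer lock is given, and the logged answering time shows that replies may be delayed.
- *That multi-dose patients are pushed to the ceiling and cannot show improvement.* The Introduction's remark on polypharmacy concerns the number of tablets prescribed, not repeated doses of one drug, and the overstatement above is partial.
- *That users learning to reply after swallowing would create a false improvement early on.* The document says nothing about answering habits. The first 14 days after installation are the preintervention phase, so learning in that period would tilt the baseline slope and could mask an effect rather than create one.

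What the reply does not remove is the ambiguity itself. The article introduces the wording as the question, not as one example. The logged delay is meant for fatigue, retention and adaptation, and it cannot show which dose a yes meant.

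**Conclusion.** The point holds as a weakness of wording and timing. For two or more daily doses of the same drug, the item can fail to record a missed later dose. For participants who reply before swallowing, it can record a dose taken shortly afterwards as not taken. Neither error is certain, and both vanish if each prompt is answered for its own dose after intake.

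The illustrated sizes, 4.5 to 12.5 points too high for the first ambiguity and 0 to 45 points too low for the second (0.90 − 0.45 at q = 0.5), rest on assumed adherence, independent doses, literal answering and a no that is never corrected. They show that the error need not be trivial among those affected. They do not estimate bias in the trial, whose size and direction the document leaves open. The point deserves attention because the item supplies the only daily adherence series and the main proximal outcome, and because the remedy is cheap.

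**What to change.** Before the pilot:

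- Reword the item to name the scheduled dose, for example 'Did you take your morning/evening dose of <medication>?', and show it for each scheduled antihypertensive dose.
- Let the answer be given or changed until that dose period has closed, so that a reply made before intake can be corrected.
- Define the daily outcome as doses taken divided by doses scheduled.
- Use the same item with the same response window in the preintervention, intervention and postintervention phases.

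The cost is a change of wording and answering window in an app still under development, plus a sentence in the outcome definition. The downside is one extra tap for multi-dose participants and a short recall delay. The planned pilot and the focus groups after it can check that participants understand the revised question.

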#### Sample Size

As a rule of thumb for an interrupted time series, 10 measurement points before and 10 measurements after an intervention provide 80% power to detect a change in level of 5 standard deviations (of the pre-data) only if the autocorrelation (ie, the extent to which data collected close together in time are correlated with each other) is greater than 0.4 [48].

According to simulations done in Liu et al [49], considering the trend change B3=0.1 (B2 + B3 = 0.25), where negative values for the parameters indicate a “decrease” (either level, trend, or both) after intervention, and positive values indicate an “increase” after intervention; autocorrelation >0.4; the Poisson time series; power >0.80; and statistical significance level of 0.05, we need at least 32 participants in the intervention group. Our plan is to recruit 100 participants to the longitudinal study, 50 in each arm due to attrition rate, specifically during the COVID-19 outbreak.

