**Methods:**

The study design is an interrupted time series. We will collect data on a daily basis, 14 days before, during 6 months of delivering digital interventions through the mobile app, and 14 days after. The effect will be analyzed using segmented regression analysis. The participants will be recruited in Region Halland, Sweden. The design of the digital interventions follows the just-in-time adaptive intervention framework. The primary (distal) outcome is MA, and the secondary outcome is blood pressure. The design of the digital intervention is developed based on a needs assessment process including a systematic review, focus group interviews, and a pilot study, before conducting the longitudinal interrupted time series study.

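### The figure of 32 participants for power above 0.80 cannot be obtained from its stated inputs, so the power claim is unsupported for the daily adherence outcome

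*Protocol article*

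**What the plan says.** The Sample Size section has two parts. The first is a rule of thumb counted in measurement points: "10 measurement points before and 10 measurements after an intervention provide 80% power to detect a change in level of 5 standard deviations". The second takes its effect from a cited simulation study, "considering the trend change B3=0.1 (B2 + B3 = 0.25" with the parenthesis closing there, and ends: "autocorrelation >0.4; the Poisson time series; power >0.80; and statistical significance level of 0.05, we need at least 32 participants in the intervention group". Recruitment is then set at 100, that is 50 per arm, with attrition as the reason but no attrition rate.

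The outcome is described elsewhere. The abstract says "We will collect data on a daily basis, 14 days before, during 6 months of delivering digital interventions through the mobile app", followed by a further 14 days. Decision Points gives the wording of the daily adherence question: "Did you take it today". Distal Outcomes adds the MUAH-16 questionnaire, before and after only, and pharmacy pickups, collected at the end. Data Collection and Analysis plans a segmented regression that tests both level and trend. Under Study Design, the control arm contributes pickups only.

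**The concern.** The 32 is the only quantitative justification of the trial's size, and it is stated as a number of people. The inputs "autocorrelation >0.4; the Poisson time series", B2 and B3 belong to one series observed over time. The section gives no baseline mean, no variance between or within participants, no number of time points for this calculation, and no time unit or link for B3. The distribution named also does not match an outcome that each person answers yes or no each day.

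At stake is how the result will be read. A null finding would be taken as coming from a study with more than 80% power, when nothing in the document shows that power for the adherence series to be analysed.

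**Working it through.** **1. Trying to reproduce 32.** Inputs from Sample Size: B3 = 0.1; B2 = 0.25 − 0.1 = 0.15; autocorrelation above 0.4 (a bound, not a value); Poisson; power above 0.80; significance level 0.05 (two-sided assumed). No standard formula turns these into a number of participants. If 32 is tried as the total number of time points in one Poisson log-link series (equal halves before and after), simulated power for B3 = 0.1 runs from 0.29 to 1.00 as the unstated baseline mean is varied from 1 to 22.4 and the unstated noise is varied. The number of participants never enters. The plan's figure is not reproduced.

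**2. Distribution.** A daily yes/no answer is bounded, with variance p(1−p). MUAH-16 is a sum of 7-point items. Neither is Poisson. Pickups could be.

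**3. Size of B3.** The section states no unit or link, so each reading is conditional. The pre-intervention trend is taken as flat.
- Log link, per day: exp(0.1) − 1 = 10.5% a day. Adherence of 50% reaches 100% in ln(2)/0.1 = 6.9 days, and 80% in ln(1/0.8)/0.1 = 2.2 days. Over 182 days the multiplier is exp(18.2) ≈ 8 × 10⁷. This cannot occur for a bounded rate.
- Log link, per week: exp(0.1 × 26) = 13.5.
- Log link, per month: exp(0.1 × 6) = 1.8, possible if baseline is below about 1/1.82 = 55%. However, 14 pre-intervention days cannot give a monthly pre-trend.
- Identity link, daily total of takers among 50: 0.1 × 182 = 18.2 people, or 36 points. This is large, but possible if baseline is below about 64%.

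**4. Illustrative power for the daily outcome.** Assumptions, none of them from the documents: baseline adherence 80%; independent days; latent between-person intraclass correlation 0.25; ordinary least-squares segmented regression on the daily proportion; two-sided 5%. The phases, 14 and about 182 days, come from the abstract. Checked with 3,000 simulated trials per case (Monte Carlo error about 1 point):

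| Change | Test | n = 32 | n = 50 |
|---|---|---|---|
| none | level or trend | 5% | 5% |
| 5-point jump | level | 31–32% | 44–45% |
| 10-point jump | level | 85% | 96% |
| 10-point gain spread over 182 days | trend | 7–9% | 7–9% |

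**5. Why the trend test is weak.** With these phases, the design matrix gives SE(level change) = 0.584σ and SE(trend change) = 0.0663σ per day. Here σ is the day-to-day SD of the group proportion, in simulation about 0.0645 (n = 32) and 0.0515 (n = 50). Stable differences between the same people drop out of σ.
- Trend at n = 50: SE = 0.0663 × 0.0515 = 0.0034 per day. The gradual gain is 0.10/182 = 0.00055 per day, about one sixth of one SE. For 80% power the trend change would have to be 2.80 × 0.0034 ≈ 0.0096, nearly one percentage point per day.
- Level at 80% power: 2.80 × 0.584 × 0.0515 = 8.4 points (n = 50) and 2.80 × 0.584 × 0.0645 = 10.5 points (n = 32). With autocorrelation 0.4 the multiplier rises from 0.58 to about 0.76, giving about 11 and 14 points.

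**6. Attrition.** Going from 32 to 50 implies a loss of 1 − 32/50 = 36%, a rate that is not stated.

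**The case against.** Several points on the other side are sound.

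- The article condenses a fuller protocol, so missing inputs may be recorded there. That would excuse silence. It does not excuse presenting a number of participants as the consequence of inputs that cannot yield one.
- Pickups may be counts, are the only measure shared by both arms, and some patients take several doses a day. The Poisson misfit is therefore limited to the yes/no series and MUAH-16. It does not by itself overstate power either, since the Poisson variance p exceeds p(1−p).
- Sizing on one coefficient while testing two is common practice and is not an error here.
- The 5-SD sentence is offered as a rule of thumb and is not the source of the 32. It still should not be used as support, because it concerns a different, very large effect and counts measurement points.

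Three stronger readings are tempting, and the documents do not support them. A reader might infer that the effect size is impossible. That holds for a daily log scale, but no unit or link is stated, and the group-total reading above allows it. A reader might infer that the stated power is false. Yet a 10-point jump exceeds 80% power at n = 32. In a separate participant-level simulation, a gradual rise from 70% to 90% had 0.78 to 0.99 power at n = 32 on a test of mean change, depending on how much individual change varied. A reader might also infer that the 32 was really a number of time points. What the cited simulations counted cannot be seen, and step 1 does not settle it.

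**Conclusion.** The concern stands in limited form. The 32 participants cannot be derived from the stated inputs, and the claim of power above 0.80 is unsupported for the daily adherence outcome. Whether true power lies above or below 0.80 depends on the effect and on quantities the document does not give. Under the assumptions in step 4, power is adequate for a 10-point jump (85% at n = 32, 96% at n = 50), poor for a 5-point jump (about 32% and 44%), and close to the type I error rate for the trend change produced by a gradual 10-point gain (7–9%). The last result is structural: it follows from a 14-day baseline and hardly changes between 32 and 50 participants. The exact percentages move with baseline adherence, between-person variation and serial correlation.

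**What to change.** Withdraw the statement that 32 participants give power above 0.80, and do not cite the 5-SD rule of thumb in support of the trial's size. In its place, with every assumption shown:

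- Give the power or detectable change of the planned 50 per arm for the binary daily series and the actual phases, separately for level and trend. Under the assumptions above, the level change detectable with 80% power is about 8–9 points at n = 50, and 10–11 points if only 32 remain. Both are larger with serial correlation.
- Say plainly that the trend-change test has little power for gradual improvement, because the pre-intervention slope rests on 14 days.
- Give the matching figure for the two-arm pharmacy-pickup comparison, which the 32 does not cover.
- State the attrition rate assumed in moving from 32 to 50, or drop that link.

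The cost is a rewritten paragraph and a short simulation. The stated power will look less favourable for small or gradual effects. No extra recruitment is asked for.
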